**Blinding**

Botulinum toxin for injection will be prepared at the pharmacy by diluting Xeomin (Merz GmBH) with 0.9% saline to a concentration of 100 mouse units (MU)/mL. As the solution is colorless and odorless, it is indistinguishable from an equivalent volume of isotonic saline which will be used for the placebo injections. The syringes with solution, either placebo or Botulinum toxin A, will be sent to the Elkie Adler Spasticity Management Clinic labeled with the subject’s code. All the investigators at the Clinic, the subject and the professional caregiver will be blinded to whether a subject received drug or placebo during the entire study. A procedure to break code will be in place at the pharmacy in case of medical emergency.

**Physical Therapy**

All study participants will receive daily stretching and passive range of motion exercises in the injected limb starting the day following injections, occurring 5 days/week (20 minutes/session), and continuing throughout the study period (32 weeks). The exercise regimen administered will consist of a program designed to maintain muscle length, facilitating gentle movements of joints to prevent contractures and permanent shortening of muscles (14). The physical therapy regimen will be taught to the professional caregiver by a physical therapist at the Clinic. At every evaluation session, the physical therapy protocol will be reinforced by the study nurse.

**DEVIATION OF FINAL PROTOCOL FROM PROTOCOL SUBMITTED TO REB**

***Based on subsequent data that was published where it was clear that physical therapy in paratonia did NOT improve outcomes, this component of the protocol was not included (***[***Int Psychogeriatr.***](http://www.ncbi.nlm.nih.gov/pubmed/22185768) ***2012 May;24(5):834-44. doi: 10.1017/S1041610211002468. Epub 2011 Dec 20.Passive movement therapy in severe paratonia: a multicenter randomized clinical trial.*** [***Hobbelen JH***](http://www.ncbi.nlm.nih.gov/pubmed?term=Hobbelen JH%5BAuthor%5D&cauthor=true&cauthor_uid=22185768)***1,*** [***Tan FE***](http://www.ncbi.nlm.nih.gov/pubmed?term=Tan FE%5BAuthor%5D&cauthor=true&cauthor_uid=22185768)***,*** [***Verhey FR***](http://www.ncbi.nlm.nih.gov/pubmed?term=Verhey FR%5BAuthor%5D&cauthor=true&cauthor_uid=22185768)***,*** [***Koopmans RT***](http://www.ncbi.nlm.nih.gov/pubmed?term=Koopmans RT%5BAuthor%5D&cauthor=true&cauthor_uid=22185768)***,*** [***de Bie RA***](http://www.ncbi.nlm.nih.gov/pubmed?term=de Bie RA%5BAuthor%5D&cauthor=true&cauthor_uid=22185768)***.)***

**Outcomes**

Assessment of outcomes will occur at baseline/screening, 2, 6, 12 and 16 weeks following injections at baseline and 16 weeks. Week 6 and 22 have been chosen as the primary endpoints, as reduction in tone due to Botulinum toxin should be well established 6 weeks following injections. Cycles of 16 weeks have been chosen as any residual effect of treatment should be worn off by this time (19).

*Outcome measures:*

*Primary Outcome*

1. **Impact on caregiver burden**: Impact on caregiver burden in providing upper extremity care will be measured by the Carer Burden Scale (22, 23). The Carer Burden Scale consists of four items (cleaning the palm, cutting the fingernails, dressing, cleaning under the armpit). Each item will be rated by the study nurse (blinded to treatment allocation) on a five point Likert scale (“no difficulty” to “cannot do task”) at each time point (baseline, weeks 2, 6, 12, and 16 following injections) for a period of 2 days and scores will be averaged. Items scored will be summed and divided by the number of items answered giving a summary carer-burden score (0 = no carer burden 4 = maximum carer burden).

**DEVIATION OF FINAL PROTOCOL FROM PROTOCOL SUBMITTED TO REB**

***As cutting fingernails was not consistently part of daily morning care in this population, it was omitted from the assessments. Since we included both left and right limbs, cleaning under the armpit and cleaning under the palm was scored for each side. As such, the total achievable score was 20. This was an oversite in the original protocol and became clear that scoring modification was required once study began.***

*Secondary Outcomes*

1. **Tone:** Tone will be assessed by the study co-ordinator using the Modified Ashworth Scale (MAS) of increased tone (7, 20). This is a 6 point scale grading the level of resistance encountered during manual passive stretching with 0=No increase in muscle tone, 1=slight increase in muscle tone, manifested by a catch and release, or by minimal resistance at the end of the range of motion when the affected part(s) is moved in flexion or extension, 2=Slight increase in muscle tone, manifested by a catch, followed by minimal resistance throughout the remainder (less than half) of the range of motion, 3=More marked increase in muscle tone through most of ROM, but affected part(s) easily moved, 4=Considerable increase in muscle tone, passive movement difficult, 5=Affected parts rigid in flexion and extension. Tone of the fingers, elbow, wrist, and shoulder abduction (depending on the muscles affected and injected) at baseline and after active and sham treatments, will be compared. A clinically significant response to treatment will be defined as at least a one point improvement from baseline in scores for muscle tone in the wrist and fingers (21).

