**Methods**

*Trial design:*

We propose a randomized, double-blind, placebo-controlled, crossover trial design. All subjects will thus act as their own controls. There will be 2 cycles of injection: at baseline and at week 16. All subjects will be randomized to receive active Botulinum toxin injection or sterile saline injections and will receive the alternate substance at the subsequent injection. The investigator assessing outcome, the study subject and the professional caregiver (primary nurse) will be blinded to treatment allocation.

*Setting:*

The Elkie Adler Spasticity Management Clinic is composed of a multidisciplinary team of physiatrists, neurologists, physical and occupational therapists, clinical nurse specialists, a social worker and a kinesiologist. There is a seating Clinic and an assistive communication device program on-site. It is located at Baycrest, in Toronto, Ontario, a geriatric-focused institution with an affiliated retirement home, nursing home and chronic-care hospital, as well as outpatient specialty Clinics. The mandate of the Clinic is to provide a multi-disciplinary team approach to patients with disabilities in order to address every aspect of their activities of daily living and to enable them to optimize their full potential to live independently and in comfort.

*Participants:*

Ten individuals with severe cognitive impairment, requiring total care for basic activities of daily living (ADLs), and having increased tone in an arm, that is interfering with the provision of care will be included in the study. If bilateral limbs are affected, only one (the more severely affected) limb will be injected.

Subjects will be eligible for the study if they have a score ≥3 (considerable resistance to passive movement) on the Paratonia Assessment Instrument (PAI) in an affected limb, and which results in one or more of: (i) difficulty in provision of morning care; (ii) postures resulting in pain when flexing, extending or abducting the limb; or (iii) postures resulting in skin breakdown or resulting in pressure ulcers. Exclusion criteria will include the presence of an alternate etiology for increased tone (ie., parkinsonian syndromes manifesting rigidity, known strokes or other focal neurological deficits), fixed contractures of the affected limb (assessed clinically as no mobility on passive range of motion), or injection with Botulinum toxin in the preceding 6 months.

*Intervention:*

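### The re-scored primary outcome rates both arms although the protocol injects only one, and its 0-20 total matches neither the defined 0-4 score nor the power statement

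*Protocol*

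**What the plan says.** **Injection rule.** Methods, Participants: "If bilateral limbs are affected, only one (the more severely affected) limb will be injected".

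**Primary outcome as defined.** Outcomes, Primary Outcome: "The Carer Burden Scale consists of four items (cleaning the palm, cutting the fingernails, dressing, cleaning under the armpit"), each rated on a five-point scale, with no side specified. The summary rule is "Items scored will be summed and divided by the number of items answered giving a summary carer-burden score", running from 0 (no burden) to 4 (maximum).

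**Primary outcome as changed.** The deviation note that follows drops one item: "As cutting fingernails was not consistently part of daily morning care in this population, it was omitted from the assessments". It then doubles two others: "Since we included both left and right limbs, cleaning under the armpit and cleaning under the palm was scored for each side". It concludes: "As such, the total achievable score was 20". The note says that the need for the change became clear after the study had started.

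**Related text.** Rationale for Study describes the toxin's action as local rather than systemic. Power calculations gives 70-80% power with 10 individuals for mean changes of 0.5 to 1.5 points on a five-point Likert scale. No deviation note alters the one-limb rule or the power statement.

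**The concern.** The Carer Burden Scale is the only primary outcome and carries the proof-of-principle objective. Two problems meet in the deviation note.

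The first is which arm is being rated. Under the protocol's own rule, one arm is injected with toxin in one cycle and saline in the other, and the second arm receives neither. Rating the palm and armpit of that second arm puts two items into the score that have no expected response to treatment. With 10 patients there is little room for such items.

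The second is the scale. The outcome is defined as a mean from 0 to 4 and reported as a total out of 20, while the detectable change is still stated in points on a five-point scale. A reader cannot set an observed change beside the change that the study was sized to detect.

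**Working it through.** **1. Reproduce the stated total.** Left and right palm, left and right armpit, and dressing make 5 items. At 0-4 each, 5 x 4 = 20, which agrees with the note. The four items as defined would have a maximum sum of 4 x 4 = 16 and a maximum mean of 4.

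**2. Items that can respond if one limb is injected.** These are the injected-side palm, the injected-side armpit and dressing, so 3 of 5. The other two belong to an arm with no injection in either cycle.

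**3. Effect on a mean and on a total.** Let each of the three items improve by d and the other two by 0.
- Mean of three items: 3d/3 = d. Mean of five items: 3d/5 = 0.6d.
- If dressing improves by only a fraction f of d, the ratio is [(2+f)d/5] / [(2+f)d/3] = 3/5, so 0.6 holds whatever f is.
- Sum of three items: 3d. Sum of five items: 3d. The absolute effect on a total is unchanged, and any loss comes through variance.

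**4. Illustrative power.** The documents give no item-level SD, inter-item correlation or alpha, so the following are assumed: n = 10, 8 degrees of freedom, two-sided 5%, d = 1, SD of each injected-arm item's within-patient difference = 1, and correlation 0.5 between all items. The SD of the uninjected-arm items, s, is varied.
- Variance of the three-item sum: 3 + 6(0.5) = 6.
- Variance of the five-item sum: 6 + (2s² + 2(0.5)s²) + 2(6)(0.5)s = 6 + 3s² + 6s.
- Noncentrality: 3 x √10 / √variance. A mean and a sum of the same items give the same value.

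| Score | s | Variance of sum | Noncentrality | Power |
|---|---|---|---|---|
| Three injected-arm items | – | 6 | 3.87 | 92% |
| All five | 1 | 15 | 2.45 | 58% |
| All five | 0.5 | 9.75 | 3.04 | 76% |
| All five | 0.25 | 7.69 | 3.42 | 85% |
| All five | 0 | 6 | 3.87 | 92% |

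Sensitivity at s = 1: with correlation 0.3 throughout, 96% against 71%; with 0.7, 87% against 48%. With 0.5 within each arm's set of items but 0 between the sets, five-item power is 79%.

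**5. Scale of the power statement.** If 0.5 to 1.5 points refers to the 0-4 mean, the same change on a five-item total is 5 x 0.5 = 2.5 to 5 x 1.5 = 7.5 points. The protocol gives no detectable change on the 0-20 scale.

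**6. If both limbs were injected.** All five items can respond and steps 2 to 4 do not apply. The injection rule was then not followed, and none of the deviation notes records it. Step 5 still applies.

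**The case against.** The deviation note gives the inclusion of both limbs as its reason for two-sided scoring. That may mean both limbs were treated, in which case nothing is diluted. The outcome is also described as burden in upper-extremity care with no side named, so a two-sided score is a defensible measure of the patient's whole care. The more severely affected limb is the one injected, so the other may sit near no difficulty and add little noise; at s = 0 the power loss vanishes. The change is openly declared, and any dilution works against the treatment. All of this stands, and it limits the point.

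A reader might infer more than the documents support:
- *The effect is diluted by 40%.* This needs the one-limb rule to have been followed, and the 0.6 factor belongs to a mean. On the declared total the effect is unchanged.
- *An unanswered item counts as zero and looks like improvement.* The note states a maximum. It does not repeal division by the number of items answered, nor say how an unanswered item is treated.
- *Nail-cutting can be restored when done.* It was left out of the assessments, so there are no data to restore.
- *The re-scoring was done with knowledge of allocation.* The Blinding section keeps all clinic investigators blinded throughout. The note does not say when or by whom the change was decided, so this is a question to answer and no evidence of a fault.

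What the objection does not remove is the conflict between the injection rule and the scoring note, or the mismatch of scales.

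**Conclusion.** The point holds in two parts.

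On either reading, the documents are inconsistent. The one-limb rule and the two-sided scoring are not reconciled, and the 0-20 total matches neither the defined 0-4 mean nor the stated detectable change, which would be 2.5 to 7.5 points on a five-item total.

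If the one-limb rule was followed, two of five primary-outcome items add noise without expected signal. A five-item mean keeps 0.6 of the injected-side effect; a total keeps the effect but generally has a larger variance. Power in the illustration is 92% for three items against 58% to 92% for five. That range rests on the assumed item effect, SDs and correlation, none of which the protocol supplies, and on no response in the uninjected arm, which is consistent with the local action the protocol describes. The protocol does not settle whether one limb or both were injected, so dilution cannot be stated as a fact.

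**What to change.** 1. State which limbs were injected, and reconcile Methods (Participants) with the deviation note on the Carer Burden Scale.
2. If one limb was injected, compute the mean of the answered items among injected-side palm, injected-side armpit and dressing, on the defined 0-4 scale and without nails. Report it beside the declared 0-20 score, labelled as defined after the study began. It should not replace the declared score: Knowledge translation records that results were presented in 2014, so a silent switch now would be made with results known.
3. State whether division by the number of items answered still applies to the 0-20 score.
4. Restate the detectable change in Power calculations on the scale actually used.
5. State whether the scoring change was decided blind to allocation.

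The cost is wording plus one re-computation, since palm and armpit were already scored by side. The downsides are small: the injected-arm score has fewer items, and there is one more analysis to report.

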To date, studies have not been performed to evaluate the efficacy of Botulinum toxin injections for paratonia. However, the profoundly detrimental impact on patient and caregiver quality-of-life as a result of immobile limbs in individuals with dementia has prompted us to offer Botulinum toxin injections to a small cohort of patients evaluated for this indication at the Elkie Adler Spasticity Management Clinic. We have found that common postures that occurred in the arm and were amenable to improvement through Botulinum toxin injections included: adducted shoulder, flexed elbow, wrist, and fingers, and a thumb-in-palm deformity, similar to postures following stroke. Such postures interfere in the provision of care and/or result in pain or skin breakdown, and diminish quality of life for patients and caregivers. Administration of Botulinum toxin in these few patients resulted in increased ease of care, decreased time to perform care, improved skin integrity, and reports of reduction in caregiver burden and patient discomfort when hygiene and morning care (defined as the period of time between 7:00 am and 12:00 pm when caregivers are engaged in activities related to bathing, grooming, dressing and toileting(16)) were administered. As such, we hypothesize that dependent individuals with dementia and increased tone resulting in involuntary postures may benefit from treatment with Botulinum toxin injections.  We propose to conduct a pilot study to test the above hypothesis, and to refine the approach to Botulinum toxin use in this context, in preparation for subsequent prospective studies.  The ultimate objective of a phase III trial would be to prove that Botulinum toxin injections are efficacious, safe and cost-effective in reducing burden of care and improving standard of care for fully dependent, cognitively impaired individuals with increased tone interfering in care.

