Muscles to be injected and exact doses injected will be determined based on the characteristics of the posture causing disability (amount of increased tone, size of muscle) using EMG-guided muscle exploration at the time of injection with an upper dose limit of 300U based on doses used in other upper-limb spasticity studies (12, 15, 17). Injection sites within the muscle will be determined according to surface landmarks for motor end-points as specified in a standard text of neuromuscular anatomy (18).

*Study procedure:*

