**Statistical Analysis**

*Power calculations*

[figure not shown]
Power calculations performed using the xsampsi application for sample size and power in crossover trials (Stata v. 11.0) were used to create the figure below. Assuming 10 unique individuals are recruited into the study, we will have 70-80% power to detect mean changes of between 0.5 and 1.5 points on a 5 point Likert scale, under different assumptions regarding the standard deviation in such measurement (SD 0.5, 1, 1.5 or 2). As such, we expect to be able to detect clinically meaningful changes in measurement with treatment even with the relatively small sample size anticipated in this pilot study. Data collection will permit further refinement of power and sample size calculations for future, larger trials if effects observed here are promising.

*Statistical Analysis*

Because of between patient variability in the affected area injected and severity of paratonia, and because of our desire to control for period and ordering effects we will use mixed regression models for analyses of quantitative outcomes, in order to isolate the effect of Botulinum toxin relative to placebo. Mixed models as applied to crossover designs permit adjustment for treatment sequences (i.e., Botulinum toxin first vs. second), period effects (i.e., first injection vs. second injection), between individual variation in severity and response to therapy, etc. We will estimate treatment fixed effects (i.e., effect of Botulinum toxin treatment), defined as the change in relevant scores from baseline to 6 weeks, and 16 to 22 weeks (i.e., change from baseline until 6 weeks post-treatment or placebo). Because of the anticipated variability in severity of paratonia in individual patients, and variability in responses of caregivers to patient disability, we will treat individual patient/caregiver dyads as model random effects.

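### The Modified Ashworth response definition counts only wrist and fingers, so a patient injected only for elbow or shoulder posture cannot be classed as a responder through the treated joint

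*Protocol*

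**What the plan says.** The Tone item under Secondary Outcomes first sets out what is compared: "Tone of the fingers, elbow, wrist, and shoulder abduction (depending on the muscles affected and injected) at baseline and after active and sham treatments". Assessment therefore follows the treated joints. The next sentence sets the response threshold, which is "at least a one point improvement from baseline in scores for muscle tone in the wrist and fingers". Elbow and shoulder do not appear in it.

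Four other places show who may be treated, and where:

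- Rationale for Study lists the postures that the clinic found treatable: "adducted shoulder, flexed elbow, wrist, and fingers, and a thumb-in-palm deformity".
- Methods, Participants: "Subjects will be eligible for the study if they have a score ≥3 (considerable resistance to passive movement) on the Paratonia Assessment Instrument (PAI"). The score is required in an affected limb, and no particular joint is named.
- Methods, Intervention: "Muscles to be injected and exact doses injected will be determined based on the characteristics of the posture causing disability".
- Statistical Analysis justifies the mixed model partly by differences between patients in the site treated: "Because of between patient variability in the affected area injected and severity of paratonia".

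The deviation note after the Tone item says that MAS was collected but not reported in the manuscript, because tone in paratonia fluctuates and the scale was judged not valid there. The note does not mention the response definition.

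**The concern.** Two adjacent sentences use different sets of joints. The first adapts to the patient, and the second fixes wrist and fingers for everyone. For a patient injected only at the elbow or shoulder, a real gain at the treated joint does not count, while a change at an untreated wrist or finger might.

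What is at stake is modest but specific to this pilot. One of its secondary objectives is to learn which outcome measures are most salient and sensitive for a later trial. A response definition that overlooks treated joints could make MAS look less sensitive for reasons of definition alone, and the definition could be carried into the successor trial.

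**Working it through.** The protocol gives no responder rate, sample size or power for MAS response, so there is no stated figure to reproduce. The check is a comparison of the text, followed by an illustration of size under assumed values.

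**Step 1: can an elbow-only or shoulder-only patient be in the trial?** Participants requires a Paratonia Assessment Instrument score of at least 3 in an affected limb, with no wrist or finger condition. Intervention selects muscles by the disabling posture. Rationale for Study includes shoulder and elbow postures among those treated. So such a patient is allowed. Nothing says that one was enrolled.

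**Step 2: how is that patient classed?** There are two possibilities, and the text does not settle which applies.

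- If MAS is recorded only at affected or injected joints, there may be no wrist or finger score, and the patient is non-evaluable.
- If wrist and fingers are scored anyway, the patient is classed on uninjected joints.

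In neither case can a gain at the treated joint produce a response.

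**Step 3: ceiling on response through a treated joint.** The input is 10 planned patients (Participants). Let k be the number injected at neither wrist nor fingers (assumed, as the protocol gives no number), and keep them in the denominator. Ceiling = (10 − k)/10.

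| k | 0 | 1 | 2 | 3 | 4 |
|---|---|---|---|---|---|
| Ceiling | 100% | 90% | 80% | 70% | 60% |

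**Step 4: effect on the active-minus-placebo contrast.** Assume a response rate pT = 0.60 at an actively treated joint and pP = 0.20 under placebo or at an untreated joint. Let q = k/10. If the k patients are classed on uninjected joints:

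- Active rate = (1 − q) × 0.60 + q × 0.20
- Placebo rate = 0.20
- Difference = (1 − q) × (0.60 − 0.20)

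| q | Active rate | Difference |
|---|---|---|
| 0% | 0.60 | 0.40 |
| 20% | 0.52 | 0.32 |
| 40% | 0.44 | 0.24 |
| 60% | 0.36 | 0.16 |

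If the k patients are non-evaluable instead, the difference stays at 0.40, but it rests on 10 − k patients: 10, 8, 6 and 4 for the same four values of q.

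With response defined on injected joints, the difference is 0.40 in all 10 patients whatever q is. These rates are illustrative and are not taken from the protocol.

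**The case against.** The strongest case on the other side has four parts.

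- **No responder analysis is described.** Statistical Analysis plans mixed models on change in score from baseline to week 6 and from week 16 to week 22. The one-point sentence can be read as a benchmark for clinical relevance, and elbow and shoulder gains enter through the score comparison. This stands, and it confines the point to the classification itself.
- **MAS was left out of the manuscript.** This also stands as a limit on practical weight. But the stated reason is fluctuating tone. The choice of joints is not mentioned, and the definition remains in the protocol uncorrected.
- **The number of affected patients may be 0.** The Rationale lists proximal and distal postures together and does not say that either occurs alone. A patient injected at both levels can still respond through wrist and fingers. This stands, so the size is unknown.
- **The statistical analysis plan might settle it.** That plan is not at hand. But the point concerns a definition that the protocol does state, and that does not fit the sentence before it.

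A reader might infer more: that elbow-only or shoulder-only patients can never be responders and so must pull down the response rate in the toxin cycle. The documents do not support this. Such a patient could be classed as a responder through a change at an uninjected wrist or finger, or could drop out of the count as non-evaluable. Nor do they support the inference that the tone comparison as a whole, or the caregiver-burden result, is distorted.

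**Conclusion.** The mismatch is real, and no other section of the protocol resolves it. Applied as written, the definition misclassifies, or cannot classify, any patient treated only at the elbow or shoulder. It affects one dichotomy on one secondary outcome in a 10-patient pilot. No planned test, power figure or primary result depends on it.

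The size depends on an unknown count. At k = 0 nothing changes. Each such patient kept in the denominator lowers the treated-joint ceiling by 10 percentage points. Under the assumed rates of 0.60 and 0.20, the responder difference falls in proportion to the share of such patients when they are classed on uninjected joints. The point deserves correction because the remedy is small and the pilot is meant to inform the choice of outcomes for a larger trial.

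**What to change.** Replace the response sentence in the Tone item with a definition per patient: at least a one-point MAS improvement, from the pre-injection visit of each cycle to 6 weeks after that injection, in the joint or joints whose muscles were injected. The new sentence should also settle these points:

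- State whether improvement in any one injected joint is enough or all must improve. The present wording leaves this open even for wrist and fingers.
- Use the same joints for a patient in both cycles, so that active and placebo are judged alike.
- Take the joints from the injection records, without reference to the MAS scores.
- If the data are already unblinded, as the recorded 2014 congress presentation suggests, label any responder result under the new definition as post hoc.

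The cost is the rewording of one definition. It needs no new measurements, provided that joint-level MAS scores and records of the muscles injected were kept; the protocol says only that MAS was collected. The small downside is that the joints counted will differ between patients, so responder rates will be less comparable with studies that use a wrist-and-finger definition. The change does not answer the separate doubt, in the deviation note, about whether MAS is valid in paratonia.
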